### Setting

Participants will be recruited from six cancer centres (and seven neighbouring district hospitals) within Yorkshire and Northumberland. National Health Service (NHS) demographic data show that Yorkshire and Northumberland have some of the highest rates of BC incidence and some of the lowest rates of survival from this cancer.^32 33^

### Recruitment

Patients will be identified through MDT meetings and approached once they know their diagnosis of HRNMIBC. This approach may be at any hospital involved in their care and by medical or nursing staff. The team will introduce the trial when treatment options are being discussed, provide the introduction leaflet and ask permission (and contact details) for a research nurse to contact the patient with more information. The number of eligible and screened patients will be recorded. Interested participants will be invited to attend an appointment at the research site and/or receive telephone calls, to be given a full explanation of the BRAVO study. Experience in similar studies suggests that patients can be overwhelmed by information given in clinic and that telephone contact can help and provides another opportunity to support patients. Up to five attempts will be made to contact the participant by telephone, after which it will be assumed they have decided to not participate. Eligible patients can be contacted by post if the immediate care team deem this best. No contact information will be shared outside of the team directly caring for the patient unless consent has been obtained.

### Consent

Informed consent takes place in a face-to-face setting at the research site. Patients will have at least 24 hours to consider participation and will be encouraged to discuss the study with their family and other healthcare professionals. A full verbal explanation of the study, a written Patient Information Sheet (detailing rationale, design and personal implications of trial entry) and informed consent form will be provided. Participants may withdraw at any stage of the trial. Consent will be obtained prior to collection of baseline assessment data and subsequent randomisation.

### Staff training

We recognise the challenge of comparing these two treatment choices and that the patient pathway includes interaction with numerous healthcare providers. To minimise bias and to maintain equipoise, a training package will be developed from interviews with patients and clinicians and delivered to staff who are likely to care for patients before and during the study. Training will incorporate lectures and role play exercises with simulated patients. A careful explanation of the potential risks and benefits of the two treatment interventions is crucial; such risks will be clearly explained to interested patients in an unbiased and fair way, assisted by written study-specific patient information.

### Randomisation

Patients will be randomised, using a 24-hour centralised telephone or web-based randomisation system, on a 1:1 basis to receive either RC or mBCG. A computer-generated adaptive minimisation algorithm that incorporates a random element will be used to ensure that the treatment groups are balanced (stratified) for:age (<75,>=75)sex (male, female)recruiting cancer centretumour stage (pTa/pTis, pT1)presence of carcinoma in situ (yes, no)previous low-risk BC (yes, no).

### Intervention: BCG immunotherapy

Maintenance BCG immunotherapy will be administered at either the cancer centre or district general hospital using the SWOG protocol.^10^ At least 12 months of BCG treatment are required, and 6 weeks of induction BCG will be followed by 3 doses at 4 and 10 months after diagnosis. Delays and deferrals are common and allowed within this study. BCG induction should include at least 4 (of 6) doses of BCG, and induction should be completed within 10 weeks. The presence of an invasive BC requires the cessation of mBCG and a change in treatment intent. Maintenance BCG may continue in the presence of low-risk NMI and HRNMI BC at the first cystoscopy; thereafter, these are managed as recurrences and require patient discussion. Rigid cystoscopy with bladder biopsy and bladder washings is mandated at the first check. After this, bladder surveillance is performed as per local protocol (flexible or rigid instruments). All cystoscopies will be undertaken or directly supervised (with a visual check) by a consultant urologist who manages HRNMIBC. Fluorescence or narrow band imaging may be used, as per local protocols. Histological review of the bladder biopsies and urinary cells should be performed to determine the presence or absence of BC.

Local and systemic complications are common in mBCG regimens and should be managed as per local protocol. The study will collect data on the frequency of expected BCG toxicities and whether this leads to the cessation of BCG treatment. Cystectomy may be performed within BRAVO for severe BCG-related toxicities, if these warrant such an intervention. Patients undergoing BCG treatment may stop treatment due to disease progression, disease recurrence, serious BCG intolerance or side effects or patient choice. Disease progression: patients who have confirmed progressive disease after any of the check cystoscopies (presence of pT2 tumours, cancer in lymph nodes or metastases) should stop BCG and be offered curative treatment for muscle invasive BC. Disease recurrence is defined as the presence of low-risk NMI or HRNMIBC from the second check cystoscopy onwards. Participants with recurrence should be offered the option of changing treatment, including RC or using second-line intravesical approaches.

### Intervention: RC

RC should be performed at each cancer centre by teams specialising in this service. Variations in surgical performance and practice produce wide differences in morbidity and mortality from RC.^34^ To mitigate these, surgeons within BRAVO will have individually undertaken at least 10 RCs per year for the last 2 years (or 20 in the last year), have median length of stay rates under 16 days and have a 90-day post-RC mortality rate of less than 10% (collected outcomes from the British Association of Urological Surgeons RC complex dataset).^31^ Postoperative complication rates and intraoperative and postoperative transfusion rates will also be taken into consideration. Individual surgeon data will act as surrogate measures for the entire surgical team and require accreditation from the trial management group before entry into BRAVO. Submitted data for surgical accreditation should reflect the practice to be undertaken within this study (eg, open or robotic approaches). Surgery should take place within 8 weeks of randomisation.

Cystectomy should include removal of adjacent organs. In males, this includes the prostate and seminal vesicles. In females, this should include a section of adjacent anterior vaginal wall, the uterus, cervix and fallopian tubes and, if no bladder reconstruction is planned, the urethra. Oophorectomy is optional, as per local practice and individualised for each patient. Pelvic lymphadenectomy is mandated within BRAVO. The template should at least include the regional lymph nodes up to the level of the ureteric crossing of the common iliac vessels. This includes the obturator fossa, the external iliac and internal iliac nodes. A more extended lymphadenectomy is acceptable. Excised lymphatic tissue should be submitted for histological analysis. Perioperative care is to be carried out as per enhanced recovery after surgery protocols.^35 36^

### Withdrawal of treatment

In line with usual clinical care, cessation or alteration of regimens will be at the discretion of attending clinicians or the participants. All participants who withdraw or are withdrawn from their allocated treatment will still attend for follow-up assessments and complete questionnaires unless unwilling to do so and outcomes will continue to be collected. In the event that a patient withdraws consent prior to randomisation, data collected up to the point of withdrawal will be analysed.

### Data collection

A screening form, to include demographic details and reasons for ineligibility, exclusion or refusal, will be completed for all patients considered for BRAVO. A feedback questionnaire will be used to identify patients who are willing to take part in the qualitative substudy (see online supplementary file 1). Baseline assessments prior to randomisation include QoL scores (EuroQuol-5D (EQ-5D),^37^ EORTC QLQ-C30,^38^ EORTC QLQ-BLM30) at trial entry.

Within mBCG, outcomes and compliance data will be collected at each cystoscopy. For RC, patient and operative data will be collected at the time of surgery, as per our national register,^31^ and then at each subsequent follow-up visit (3, 6 and 12 months postrandomisation). Follow-up imaging (CT scan) to assess response to treatment will be performed in both arms at 1-year postrandomisation. QoL questionnaires will be collected at 3, 6 and 12 months postrandomisation in face-to-face consultations or by telephone. These include EQ-5D,^37^ EORTC QLQ-C30^38^ and either EORTC QLQ-BLM30 (for those randomised to RC) or EORTC QLQ-NMIBC24 (for those randomised to BCG). Information will be collected on deaths, complications and toxicities (adverse events) and related and unexpected serious adverse events up to 1 year postrandomisation or 3 months after the last participant is randomised if earlier.

### Statistical analyses

A detailed statistical analysis plan will be written before any analysis is undertaken. All analyses and data summaries will be conducted on the intention-to-treat population. No formal interim analyses are planned, and final analysis will take place when all available data have been received. The analysis will focus on descriptive statistics and CI estimation. Primary analysis will include summaries of the number of patients at each stage of the recruitment pathway (screening, eligibility, consent and randomisation) and assessment of the overall monthly recruitment rate. Secondary analysis will include summaries of acceptance of randomised treatment and mBCG treatment compliance. Participant retention and self-reported QoL outcomes during follow-up, including withdrawal data (timing and reason), will also be summarised overall and by time point. Levels of missing data in QoL outcomes will be assessed. The median cancer-specific survival estimate and its corresponding 95% CI will be calculated to inform the sample size calculation of the phase III trial. As this is to aid the design of a pragmatic phase III trial, all randomised patients will be included in the calculation, regardless of treatment received. Cancer-specific survival will be calculated from the date of randomisation to the date of cancer-specific death. Participants with missing follow-up data or who are alive at the time of the analysis will be censored at the date they were last known to be alive. Overall survival, calculated from the date of randomisation to the date of death, will also be summarised as for cancer-specific survival.

The frequent collection of QoL data within this feasibility study is necessary in order to assess the burden to patients. This will be assessed by monitoring collection compliance rates and will inform the optimal frequency of data collection for the main trial. Averaged QALYs may be a coprimary endpoint for the main trial; as such, determining the optimal frequency of EQ-5D data collection within this feasibility study is crucial.

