### Study aims

Our aims are to assess whether a larger phase III RCT is possible and to acquire sufficient 129 data to aid planning such a trial. Primary outcomes are: To assess the number of patients screened and identified as eligible within these six centres.To assess recruitment rates (number of patients randomised per month).

Secondary outcomes are:To assess acceptance of allocated treatment.To assess the rate of compliance with mBCG at 12 months after randomisation and collect reasons for non-compliance.To assess the feasibility and optimal frequency of collecting QoL data in patients treated for HRNMIBC.To obtain preliminary data on the QoL data of patients treated for HRNMIBC.To explore the reasons expressed by patients for declining recruitment into the study.

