### Safety

The number of adverse events and related unexpected serious adverse events will be summarised descriptively by arm, grade and body system. The proportion of participants experiencing each toxicity will be summarised by maximum National Cancer Institute’s Common Terminology Criteria for Adverse Events grade^39^ experienced, overall and by arm. Operative RC complications will be graded using the Clavien Dindo classification.^40^

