### Qualitative substudy design

All eligible patients will be asked to complete a questionnaire to gauge their understanding of BRAVO and their views on the recruitment process. We will collect data from patients who decline the study, who consent but refuse allocation and who consent and accept allocation. A short questionnaire will be given to seek patient views on the recruitment process and to ask if participants would be willing to provide detailed feedback by face-to-face or telephone interview. A purposive sample of 15 patients will be selected for interview. Written consent will be taken prior to the interview and a flexible topic guide developed in conjunction with patient and public involvement (PPI) representatives, clinical colleagues and informed by the literature used to assist questioning. The topic guide will be devised to ensure that the key issues are covered but do not dictate data collection and will be flexible enough to elicit participants’ own experiences and views of the trial as well as issues unanticipated by the interview team. Interviews will be audio-recorded, transcribed and anonymised to protect confidentiality. With their consent, participants may be contacted after the interview to answer questions that may emerge during the analysis or to explore issues that emerged in the interviews in more depth.

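### Harms would be tabulated by allocated arm, because intention-to-treat governs every summary and no treatment-received population is defined, although the protocol expects departures from allocation

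*Protocol article*

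**What the plan says.** The protocol article, Statistical analyses, sets one population for everything: "All analyses and data summaries will be conducted on the intention-to-treat population". The section also explains why patients stay in whatever they received, but gives that reason for the survival estimate only, as an aid to designing a pragmatic phase III trial.

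The Safety section then states: "The number of adverse events and related unexpected serious adverse events will be summarised descriptively by arm, grade and body system". The proportion with each toxicity, by maximum CTCAE grade, is to be given as "experienced, overall and by arm". For surgery it adds: "Operative RC complications will be graded using the Clavien Dindo classification". No safety, treated or as-received population appears anywhere in the article.

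Several sections expect allocation and treatment to differ:

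- Study aims makes acceptance of the allocated treatment a secondary outcome.
- Qualitative substudy design plans to collect data from patients "who consent but refuse allocation and who consent and accept allocation".
- Withdrawal of treatment keeps patients who leave their allocated treatment in follow-up, with outcomes still collected.
- The BCG intervention section allows cystectomy for severe BCG toxicity and names RC among the options at recurrence.

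**The concern.** Intention-to-treat suits outcomes that describe the effect of a treatment policy. It is a poor sole basis for describing harm when the two treatments have largely different toxicities and some patients will not receive the one they were allocated. A patient allocated to RC who chooses BCG and develops BCG toxicity is counted against RC. A patient allocated to mBCG who has surgery instead carries operative morbidity into the mBCG column. Patients who never receive a treatment still sit in the denominator of its arm and pull its toxicity rate down.

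At stake is the per-treatment harm description. The BCG intervention section says the study will record how often expected BCG toxicities occur, and an allocated-arm table does not give that frequency among people who had BCG. With 30 patients per arm, a handful of departures changes the percentages visibly.

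**Working it through.** The plan gives no figure of its own on this point. Its only formal calculation, the phase III sample size of 506, does not bear on it. The check is a reading of the text followed by an illustration.

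**Reading.** The intention-to-treat sentence is unqualified. The Safety section does not define arm as treatment received. The Data collection section assigns the bladder-specific questionnaires by randomised treatment, which fits arm meaning allocation. Followed as written, the toxicity tables are by allocation.

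**Inputs.**

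- 30 patients per arm (Discussion).
- BCG toxicity of 74% (Current knowledge).
- Share c of each arm that takes the other treatment: not in the documents. Assumed 10% and 20%.
- Simplification: BCG toxicity occurs only in patients who receive BCG, at the same rate whichever arm they were allocated to.

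**Formulas.**

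- BCG toxicity shown in the mBCG arm = 30 × (1 − c) × 0.74 / 30
- BCG-toxic patients listed under RC = 30 × c × 0.74

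**Results.**

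| Assumed c | Shown in mBCG arm | BCG-toxic patients under RC | As share of RC arm |
|---|---|---|---|
| 0% | 74% | 0 | 0% |
| 10% | 27 × 0.74 / 30 = 66.6% | 3 × 0.74 = 2.2 | 2.2 / 30 = 7.4% |
| 20% | 24 × 0.74 / 30 = 59.2% | 6 × 0.74 = 4.4 | 4.4 / 30 = 14.8% |

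**By treatment received**, at c = 20%: BCG recipients are 24 + 6 = 30, of whom 17.8 + 4.4 = 22.2 have toxicity, and 22.2 / 30 = 74%.

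**Other patterns.** If only the RC arm departs, the mBCG arm still shows 74%, but 7.4% to 14.8% of the RC arm carries BCG toxicity. If those who refuse take neither treatment, the mBCG arm is diluted as in the table and nobody is misplaced under RC.

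**The overall column** does not recover the rate. With equal departures in both arms it reads 30 × 0.74 / 60 = 37% whatever the value of c, because it divides by everyone randomised.

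**The case against.** The strongest reply is that the Safety section leaves arm undefined, that a detailed analysis plan is promised, and that safety populations are often settled there. That would answer a complaint about silence. Here the protocol states a universal rule, and an analysis plan must either follow it or depart from it.

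Several other objections do stand, and they limit the point:

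- **Recruitment counts.** A reader might infer that the primary analysis is impossible, since unrandomised patients cannot belong to an intention-to-treat population and one primary aim is "To assess the number of patients screened and identified as eligible within these six centres". The documents do not support a consequence. Data collection requires a screening form for all patients considered, Statistical analyses lists the pre-randomisation stages explicitly, and the progression criterion is set among eligible patients. These specific provisions plainly govern and no number would change. This is wording only.
- **Operative complications.** A reader might infer that refusers dilute the surgical complication rate, for example from 20% to 16% (24 × 0.20 / 30). The Safety section gives no denominator for the Clavien-Dindo grading, and operative data are collected at the time of surgery. The denominator needs stating, but a diluted one is not in the text.
- **Recognisability.** Toxicities are tabulated by type and grade, surgical complications have their own scale, and acceptance and compliance are reported. Many events will still be recognisable as BCG-related or surgical, so it would be too strong to say that the tables hide the cause. What is lost is the correct rate per treatment.
- **Cystectomy after BCG.** Reporting this under mBCG is informative about the mBCG strategy, which is a reason to keep the by-allocation table.
- **Weight.** Study aims lists no harm outcome, the progression criteria contain none, and all analyses are descriptive.

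**Conclusion.** The point holds for adverse event and toxicity summaries. As written, they follow allocation in a study that expects some patients not to receive what they were allocated, and no summary by treatment received is provided for. The illustrated effect is a 74% BCG toxicity rate appearing as about 67% to 59% in the mBCG arm, with about 2 to 4 BCG-toxic patients listed under RC. That rests on an assumed 10% to 20% in each arm taking the other treatment, and on the literature rate applying equally to everyone who has BCG. The true size is unknown until acceptance is observed, and it is nil if everyone receives their allocated treatment.

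The point does not reach the recruitment analysis, the progression decision or the survival estimate. It is a worthwhile and inexpensive correction to a stated rule, not a threat to the study's primary aims.

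**What to change.** In Statistical analyses, limit intention-to-treat to acceptance of allocation, retention, quality of life and survival. In Safety, add that:

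- adverse events and toxicities are summarised by treatment actually received: patients with at least one BCG instillation, and patients in whom RC was performed;
- a patient who receives both contributes each event to the treatment most recently started before its onset, since the two groups overlap and need an assignment rule;
- events before any treatment are listed separately, so that those arising between randomisation and surgery are not lost;
- Clavien-Dindo complications use patients who underwent RC as the denominator;
- the by-allocation table is kept alongside, with a statement that the treatment-received groups are not randomised comparisons.

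The cost is a few sentences and one extra set of descriptive tables. The safety collection window, which runs from randomisation, need not change. The trial team should confirm that treatment start dates are recorded for patients who do not follow their allocation. The price in interpretation is that patients who choose their treatment may differ from those who accept allocation, which is why both tables are needed.

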## Methods and design

### Trial design

BRAVO is a multi-centre, parallel-group, mixed-methods, individually randomised, controlled feasibility study in patients with HRNMIBC suitable for treatment by either mBCG or RC. Eligible, consenting patients will be randomised (1:1) to receive either mBCG or RC (figure 1). Due to the different treatment modalities in the two arms, it is not feasible to blind patients or clinicians to treatment allocation. Patient reported outcome data will be collected at 3, 6 and 12 months postrandomisation in clinic or by postal questionnaire if the patient is not due to attend a clinic visit.

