### Sample size

The sample size for this feasibility study has been set to give confidence that the recruitment target for the main trial can be met. A formal power calculation is not appropriate as effectiveness is not being evaluated. It is estimated that, per year, over the six centres, there will be approximately 1000 new diagnoses of NMIBC, where 20% are likely to be eligible (200 patients).^31^ We would need to show that we are able to randomise approximately 25% of all eligible patients to be confident that the recruitment target for the main trial would be met within 3 years, with an additional nine centres. We therefore plan to recruit 60 patients over an 18-month period in the feasibility study. For the phase III trial, we anticipate either a single primary endpoint (cancer-specific survival) or coprimary endpoints (cancer-specific survival and averaged quality-adjusted life years (QALYs)). We estimate that 506 participants are required to have 80% power to show a superiority HR of 0.626 (based on an improvement in 5-year cancer-specific survival from 70% in the BCG arm to 80% in the RC arm), assuming a 3-year accrual period, 5 years of follow-up and accounting for 5% loss-to-follow-up.

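### Median cancer-specific survival is planned as an input to the phase III sample size, but with at most 12 months of follow-up it will not be reached

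*Protocol article*

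**What the plan says.** The Statistical analyses section names the statistic and its purpose: "The median cancer-specific survival estimate and its corresponding 95% CI will be calculated to inform the sample size calculation of the phase III trial". It defines the analysis set by saying that "all randomised patients will be included in the calculation, regardless of treatment received". Anyone still living or lost to follow-up is censored at the latest date of known survival. Overall survival is to be summarised as for cancer-specific survival. No survival summary at a fixed time is named.

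Under Data collection, information on deaths is gathered "up to 1 year postrandomisation or 3 months after the last participant is randomised if earlier". No longer survival follow-up is described anywhere in the article.

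The Sample size section sets the size and pace of the study: "We therefore plan to recruit 60 patients over an 18-month period in the feasibility study". Trial design gives the allocation: "Eligible, consenting patients will be randomised (1:1) to receive either mBCG or RC". The phase III calculation (506 participants, HR 0.626, 80% power) rests on "an improvement in 5-year cancer-specific survival from 70% in the BCG arm to 80% in the RC arm".

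**The concern.** A Kaplan-Meier median exists only if the curve falls to 50% while patients are still under observation. On the protocol's own assumptions, at least 70% of patients in either arm have not died of bladder cancer at five years, yet observation stops at one year. The plan has therefore fixed an estimator that cannot be obtained from the data it will collect, and has given that estimator a design role.

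The practical result would be a line reading 'not reached' with no interval, so the survival input promised for phase III planning would be empty. Overall survival meets the same obstacle unless about half of the participants die of any cause within a year, which nothing in the article suggests.

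**Working it through.** **Inputs from the protocol article.** 60 patients, 18-month accrual, 5-year cancer-specific survival (CSS) of 70% and 80%, HR 0.626, 80% power, 3-year phase III accrual, 5 years of follow-up and 5% loss (Sample size); 1:1 allocation (Trial design); deaths collected to 12 months, or to 3 months after the last randomisation if earlier (Data collection).

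**Assumptions added here.** Exponential survival; uniform accrual; all 60 recruited; two-sided 5% alpha for phase III, which the article does not state.

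**1. Reproduce the phase III figure.**
- HR = ln(0.8)/ln(0.7) = 0.6256, which agrees with 0.626.
- Freedman events = (1.960 + 0.842)² × (1.626/0.374)² ≈ 148.4, rounded up to 149.
- Event probability per arm = 1 − [exp(−5λ) − exp(−8λ)]/(3λ). The mean over the two arms is 0.3105.
- 149/0.3105 gives 480, and 480/0.95 gives 506.

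The stated 506 is reproduced exactly. The phase III calculation is not in question, and the survival model used below is the one behind it.

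**2. Hazards, medians and 12-month survival.**

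| | BCG | Cystectomy |
|---|---|---|
| Hazard per year, −ln(S5)/5 | 0.0713 | 0.0446 |
| Median, ln 2/hazard | 9.7 years | 15.5 years |
| 12-month CSS, exp(−hazard) | 93.1% | 95.6% |

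The mean of the two 12-month figures is 94.4%.

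**3. Follow-up available.** For entry at month t, follow-up is min(12, 21 − t) months. The first half of accrual gets 12 months. The second half falls from 12 to 3, averaging 7.5. The mean is (12 + 7.5)/2 = 9.75 months, and 60 × 9.75/12 = 48.75 person-years.

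**4. Expected cancer deaths.** Averaging 1 − exp(−hazard × follow-up) over entry times gives 2.75 deaths among 60. If everyone had a full 12 months: 30 × (1 − 0.9311) + 30 × (1 − 0.9564) ≈ 3.4.

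**5. Is the median reached?** In 30,000 simulated trials under these assumptions, the Kaplan-Meier curve fell to 50% in none. The lower 95% limit for the median was never reached either. There was no cancer death at all in 5.8% of trials.

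**6. Stress tests (10,000 simulated trials each).**
- 5-year CSS of 50% in both arms: 6.4 expected deaths; median never reached.
- CSS of 37% at 3 years in everyone (the figure under Current knowledge for tumours failing mBCG): 14 expected deaths; median reached in 0.05% of trials.

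**7. What about three deaths can support.** For 3 deaths in 48.75 person-years the exact Poisson 95% CI for the rate is 0.0127 to 0.180 per year. As 12-month CSS this is exp(−0.180) to exp(−0.0127), about 84% to 99%. Carried to five years it is 41% to 94%. The exponential median would be 11.3 years, 95% CI 3.9 to 55.

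**The case against.** The strongest reply concerns importance. Cancer-specific survival is not among the primary or secondary outcomes under Study aims. The progression criteria rest on recruitment and follow-up rates and on randomising at least 20% of eligible patients, and the feasibility sample size does not use survival. The phase III assumptions are already set without survival data from this study. All of this stands, and it limits the consequence to one uninformative survival summary.

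A second reply is that the counts depend on a model. The article states neither exponential survival nor uniform accrual, and slower recruitment would lower the counts. That is true, but the conclusion does not rest on the exact count: a curve expected near 94% at 12 months is far from 50%. The censoring rule might suggest longer observation, but none is stated, and following everyone to month 21 still gives only about 3.4 deaths.

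Some stronger readings are tempting but not supported:

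- *The study cannot inform phase III.* Only the survival input fails. The Statistical analyses and Discussion sections also use the study for eligible numbers, acceptance of allocation and quality-of-life/EQ-5D collection.
- *The arms will be pooled.* The wording on including all randomised patients most naturally describes the intention-to-treat set. It does not say that the arms are combined, and an analysis plan would normally settle presentation by arm.
- *A misleading extrapolation is planned.* The protocol proposes no parametric extrapolation. Step 7 of the working only shows that one would not rescue the median.
- *The cancer-specific survival definition is at fault for lacking a competing-risks method.* No error in the definition is shown, and with about three deaths the choice would change little.

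**Conclusion.** The point holds, at moderate weight. The planned median and its 95% CI will not be obtained from follow-up of 3 to 12 months when the protocol's own survival figures place the medians about 10 to 15 years out. About 3 cancer deaths are expected (2.75 with the stated cut-off, 3.4 with a full year for everyone), assuming exponential survival, uniform accrual and 60 recruits. The failure of the median survives much worse prognosis, as the stress tests show. The same applies to overall survival unless all-cause mortality is near one half within a year. The feasibility outcomes, the progression decision and the phase III figure of 506 are unaffected.

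**What to change.** In Statistical analyses, replace the median with Kaplan-Meier estimates of cancer-specific and overall survival at 12 months, each with a 95% CI. Add the number of deaths, the person-time, and the death rate with an exact CI. Label all of these descriptive. Present them preferably by arm as randomised, because the phase III calculation needs a control-arm rate. Show the number at risk: with uniform accrual and the stated cut-off, only about half of the participants (those entering in the first 9 of 18 months) can be followed to 12 months.

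Add a sentence saying that the phase III survival assumptions will rest on longer-term external data, while this study continues to inform recruitment, acceptance of allocation, retention and quality-of-life/EQ-5D collection.

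The cost is a few sentences, carried into the statistical analysis plan before any analysis. No additional data are needed.
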